**RESEARCH PLAN**

We will perform the clinical studies at i) Alexishafen and Mugil Clinics, Madang Province, sites we have used for various studies since 2001 and which have proven recruitment potential and excellent facilities,CIA#31 and ii) Vunapope Hospital, East New Britain Province which also has a busy clinical load and laboratories which have been used by the PNG Institute of Medical Research (IMR) for malaria studies. Maprik in the East Sepik may be brought in as an additional site depending on recruitment. Laboratory studies (host/parasite genotyping, drug assays and/or biochemical testing) will be conducted at Vunapope; the IMR laboratories at Yagaum Hospital, Madang Province; the University of Western Australia (UWA) School of Medicine and Pharmacology and the Biochemistry Department at Fremantle Hospital; the Pharmacy School, Curtin University. Relevant techniques are well established in these institutions.

**Main Study: A trial of the tolerability, safety, efficacy and cost-effectiveness of AL, AP and AN in PNG children with uncomplicated falciparum or vivax malaria** *(Primary aim)*

*Background:* Since pyronaridine11-14 and naphthoquine16 are active against CQ-resistant falciparum malaria and have a t½*e* that is at least that of lumefantrine (4-6 days), AP and AN should have similar efficacy over 42 days of follow-up to AL in this situation. We postulated that the greater efficacy of DP vs AL against *P. vivax* reflects, in part, the longer piperaquine t½*e* (3-4 weeks), in which case the efficacy of AP and perhaps AN should equate with that of DP. However, the similar low efficacy of AL and CQ-SP in areas with known CQ-resistant *P. vivax* means that other factors may underlie the poor response to AL in our recent trial.8

*Operational principles:* We will conduct the study using standard operating procedures, under Good Clinical Practice guidelines, in accordance with the Helsinki Declaration, and with ethical approval from the PNG Ministry of Health Medical Research Advisory Committee and the UWA Human Research Ethics Committee. Although the trial is open-label, there will be an independent Data and Safety Monitoring Committee (DSMC) and external monitoring of sites.

*Endpoints:* The primary endpoint will be:

1. recrudescent *P. falciparum* within 42 days after correction for re-infections using PCR genotyping of polymorphic parasite loci19, 20 in children with falciparum malaria, or

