2. appearance of any *P. vivax* parasitaemia within 42 days after treatment for vivax malaria.

Secondary endpoints in falciparum malaria will be:

1. reappearance of PCR-uncorrected *P. falciparum* parasitemia,
2. appearance of any *P. vivax* parasitemia, and
3. appearance of *P. falciparum* gametocytes, all within 42 days.

Secondary endpoints in vivax malaria will be:

1. reappearance of any *P. vivax* parasitemia within 28 days, and
2. appearance of *P. vivax* gametocytes within 42 days.

Other secondary endpoints for each *Plasmodium* species will be initial fever and parasite clearance times (the times to the first of two consecutive assessments at which the child was afebrile and slide-negative, respectively), and drug safety including haemoglobin levels.

*Sample sizes:* Sample size calculations21 for the present trial are based on the assumptions that i) the *P. falciparum* Day 42 PCR-corrected ACPR for AL is 95.2%8 with a non-inferiority margin of 5% for AP and AN, ii) the *P. vivax* Day 42 uncorrected ACPR for AP and AN is at least double the 30.3% found previously for AL (as for DP in the original trial8), iii) there will be equal numbers in each treatment arm, and iv) there will be a 25% attrition rate:

| Study | Type | Total *n* | *n*/group with drop-outs | Power | Α |
| --- | --- | --- | --- | --- | --- |
| *P. falciparum* | Non-inferiority | 515 | 220 | >80% | 0.05 (one-tailed) |
| *P. vivax* | Superiority | 122 | 60 | >90% | 0.05 (two-tailed) |

*Subjects:* Children aged 0.5-5 years with an axillary temperature >37.5°C or fever during the previous 24 hours will be screened using on-site blood film microscopy. Those with either *P. falciparum* (>1000 asexual parasites/μL whole blood) or *P. vivax* (>250/μL) will be eligible if they have i) no features of severity,22 ii) not taken a study drug in the previous 28 days, iii) no clinical (including anthropometric) or laboratory evidence of another infection or co-morbidity including malnutrition. Informed consent will be obtained from parents/guardians.

*Clinical/laboratory procedures:* An initial (Day 0) history will be taken and physical examination performed. Blood will be taken for measurement of haemoglobin and glucose. Treatment allocation will be by computer-generated randomized design in blocks of 24 by site:

1. AL (Novartis Pharma, Basel, Switzerland) as artemether 1.7 mg/kg and lumefantrine 10 mg/kg twice-daily for three days,

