*Interim analysis:* Although the AN regimen to be used in the trial has been developed using detailed efficacy and safety assessment, a validated assay and conventional pharmacokinetic modelling in PNG children, we will perform an interim analysis after the first 50 children have received this form of treatment. This analysis will be done by the Data and Safety Monitoring Committee ([name] (UPNG), [name] (UWA) and [name] UWA – statistician) who will decide whether the AN arm should be retained for the rest of the trial. The criteria to be used will be i) day 3 parasitaemia positive >25% of children, ii) gametocyte carriage >25% on day 7 and/or iii) >25% attrition rate by day 7.

If AN is withdrawn, children in this arm will be switched to DP (dihydroartemisinin 2.5 mg/kg and piperaquine phosphate 20 mg/kg daily for three days; Sigma Tau, Rome, Italy) given with milk at each dose. DP was one of the arms in our original treatment trial8 and is currently recommended second-line treatment in PNG for uncomplicated malaria in children. However, there has been the suggestion that cure rates might improve if fat were co-administered with this form of ACT to enhance bioavailability,28 as it is with AL. As per the Manufacturer’s instructions, DP was administered with water in the original trial.8 All study procedures will remain the same for children in this group.

*Data analysis:* Statistical analysis will be by *a priori* plan. Per-protocol analyses will include children with complete follow-up or a confirmed treatment failure, and will exclude those treated for malaria without confirmatory microscopy or who defaulted from follow-up despite repeated attempts at contact. These excluded patients will be retained in modified intention-to-treat analyses utilizing:

1. a worst-case approach (ETF assumed for Day 3 exclusions, LPF/LCF otherwise) and
2. a best-case approach (all missing blood films assumed parasite-negative).8

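### The two modified intention-to-treat rules treat missing children alike in every arm, so they bound each arm's cure rate but not the AP/AN minus AL difference on which P. falciparum non-inferiority rests

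*Protocol*

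**What the plan says.** All of this is in the protocol's Research Plan, under the Main Study.

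- **Sample sizes.** The falciparum comparison assumes "Day 42 PCR-corrected ACPR for AL is 95.2%8 with a non-inferiority margin of 5% for AP and AN", and "there will be equal numbers in each treatment arm". It also assumes that "there will be a 25% attrition rate", a single figure not split by arm. The table row reads "Non-inferiority | 515 | 220 | >80% | 0.05 (one-tailed".
- **Endpoints.** The falciparum primary endpoint is recrudescence "within 42 days after correction for re-infections using PCR genotyping".
- **Data analysis, per-protocol set.** "Per-protocol analyses will include children with complete follow-up or a confirmed treatment failure". Defaulters and children treated for malaria without a confirming film are left out.
- **Data analysis, modified intention-to-treat.** The excluded children come back in two ways: "a worst-case approach (ETF assumed for Day 3 exclusions, LPF/LCF otherwise" and "a best-case approach (all missing blood films assumed parasite-negative".

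Neither rule depends on the treatment arm.

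**The concern.** The labels worst case and best case suggest a bracket: if the conclusion survives both, missing data cannot have produced it. That is true of a single arm's response rate. It is not true of a difference between arms, because giving missing children the same outcome in both arms pulls the arms together when losses are similar. In a superiority comparison that pull is cautious. In a non-inferiority comparison it favours the claim.

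The planned attrition is 25% and the margin is 5 points. A reader could take a modified intention-to-treat result as independent support for non-inferiority when, under the plan's own attrition figure, it is the more lenient test.

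The per-protocol set has its own selection: a child with partial follow-up stays in only by failing.

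**Working it through.** **The plan's own figure.** At 95.2% in both arms, margin 0.05, one-sided 0.05 and 80% power, the unpooled Wald formula gives (1.645 + 0.842)² × 2 × 0.952 × 0.048 / 0.05² ≈ 226.0, so 227 per arm. With the restricted-null (Farrington-Manning) variance it is 254 per arm. That is 508 for two arms, so 515 fits within 3% as a two-arm total. The 220 per group does not reproduce: 227/0.75 = 303, 254/0.75 = 339, and 515/3/0.75 = 229. I take 220 as printed. I also check 230, because 3 × (230 + 60) = 870 matches the recruitment target under Duration/feasibility, whereas 3 × (220 + 60) = 840.

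**Set-up.** AL success is 0.952 and test-drug success is 0.902, exactly at the margin. Loss d is independent of outcome. With p the true success rate, observed success is:

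- worst case: (1 − d)p
- best case: (1 − d)p + d

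**Equal loss, d = 0.25**

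| Set | AL | Test | Deficit |
| --- | --- | --- | --- |
| Per-protocol | 95.2% | 90.2% | 5.00 |
| Worst case | 71.4% | 67.65% | 3.75 |
| Best case | 96.4% | 92.65% | 3.75 |

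The true 5 points lie outside both modified results.

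**False non-inferiority rate**, Φ[(0.05 − deficit)/SE − 1.645], 220 per arm:

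- Worst case: SE = √[(0.714×0.286 + 0.6765×0.3235)/220] = 0.0439. Φ(0.285 − 1.645) = 8.7%.
- Best case: SE = √[(0.964×0.036 + 0.9265×0.0735)/220] = 0.0216. Φ(0.578 − 1.645) = 14.3%.
- Per-protocol (165 per arm): 5.0% by construction.

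In 400,000 simulated trials the rates were 8.7% (worst), 16.1% (best) and 5.7% (per-protocol). At 230 per arm the formula gives 8.8% and 14.6%. At 10% loss it gives 6.6% and 7.6%.

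**Loss spread over the 42 days.** If failures seen before loss are counted, the best-case deficit is about 4.0-4.3 points (shrinkage 14-21%) and its rate is 9-12%. The worst-case deficit stays near 3.75. So 16% is an upper figure for the best case.

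**Unequal loss, 220 per arm (formula)**

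| Loss AL / test | Worst-case deficit, rate | Best-case deficit, rate |
| --- | --- | --- |
| 25 / 26.4% | 5.01, 5.0% | 3.61, 15.9% |
| 22 / 28% | 9.31, 0.4% | 3.31, 19.5% |
| 28 / 22% | −1.81, 46% | 4.19, 10.2% |

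The worst case follows the balance of attrition more than efficacy. The best-case deficit is 0.098(1 − d_test) − 0.048(1 − d_AL). This stays below 5 points unless AL loss exceeds about twice the test-arm loss (0.098/0.048 = 2.04).

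**Joint use, equal 25% loss (simulated).** Per-protocol and best case both passing: 5.7%, the same as per-protocol alone. All three passing: 1.9%. With truly equal drugs, the power is about 69% per-protocol, 32% worst case and 88% best case.

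**Per-protocol selection.** Assume 25% loss, uniform over Days 0-42. With failures uniform over Days 14-42, the mean failure day is 28, so a child due to be lost has gone before failing with probability 28/42 = 0.667.

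- Failures seen: 0.048 × (1 − 0.25×0.667) = 0.040.
- Children excluded: 0.25 − 0.048×0.25×0.333 = 0.246.
- Failure rate: 0.040/0.754 = 5.3%, against a true 4.8%.

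Failures uniform over Days 0-42 give 0.042/0.756 = 5.6%. Failures confined to Days 28-42 give 0.038/0.752 = 5.1%.

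**The case against.** The strongest case on the other side has four parts.

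1. **The rules have a proper use.** They bound each arm's response, which matters because the Background cites an absolute WHO requirement of over 95%. The protocol nowhere says that they bound the treatment difference. This stands; the point is only that they cannot serve the comparison.
2. **Nothing makes modified intention-to-treat decisive.** A reader might infer that the trial's false non-inferiority rate is raised, or that agreement between sets raises it. The documents do not support either. Per-protocol analysis is listed first, and requiring agreement never takes the error above per-protocol alone. This stands. What remains is that the best case adds no check: in the simulations it never overturned a per-protocol pass.
3. **The quarter is not built into the rules.** It is the planned attrition carried through under equal loss. About 1.4 points more loss in the test arm restores the full 5 points under the worst case. The Interim analysis paragraph itself contemplates heavy loss in the AN arm. This stands, and it makes the worst case unpredictable rather than safe.
4. **The data from partly followed children are not simply discarded.** A reader might infer that Kaplan-Meier never uses their films. The best-case rule fills in only missing films, so those obtained remain, and the protocol does not tie Kaplan-Meier to one set or forbid censoring. That reading should not be made.

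A tipping-point analysis could also be left to the statistical analysis plan, which is not shown. But the two symmetric rules are already fixed in the protocol.

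**Conclusion.** The concern holds for the P. falciparum non-inferiority comparison, within limits. The two rules do not bracket the AP/AN minus AL difference. With equal 25% loss unrelated to outcome, both dilute a 5-point deficit by up to a quarter. A test on one of those sets alone then has a false-positive rate of about 9% (worst case) or up to 16% (best case; 9-12% when failures before loss count). With unequal loss the worst case can be very strict or very lenient. The best case leaned towards non-inferiority in every scenario tried.

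The per-protocol failure rate is raised by its selection rule, from 4.8% to about 5.3-5.6% for failures spread over most of follow-up, and less if they come late.

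The size rests on the planned attrition, loss independent of outcome and a Wald test. Trial-level error is inflated only if a modified intention-to-treat result alone can carry the claim. For P. vivax superiority, dilution from equal loss is conservative. The point deserves correction but does not undermine the trial.

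**What to change.** 1. State that non-inferiority will not be claimed on a symmetric-imputation modified intention-to-treat result alone.
2. Add the Kaplan-Meier Day 42 difference, with its confidence limit, on all treated randomised children, censored at the last available film. This uses partial follow-up without assigning an outcome and avoids keeping early leavers only when they fail.
3. Replace or supplement the two symmetric rules with a tipping-point analysis over arm-specific missing outcomes, reporting how many more failures among missing AP or AN children than among missing AL children would overturn the conclusion.
4. Use the arm-specific extremes only as the ends of that analysis. With equal true efficacy of 95.2% and 25% loss, counting missing AL children as successes and missing test-arm children as failures shows 0.75 × 95.2 + 25 = 96.4% against 0.75 × 95.2 = 71.4%. That 25-point gap could never meet a 5-point margin, so it cannot be a decision rule.

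The symmetric rules may stay as descriptions of each arm's response rate. The cost is protocol or analysis-plan wording and a little more analysis, with no new data. The drawback is that the extremes will be wide if attrition reaches 25%.

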At baseline and each subsequent visit, a finger-prick blood smear and filter paper blood spot will be taken, in addition to a 250 μL mixed capillary EDTA sample which will be centrifuged and the plasma separated. In addition, a 3-5 mL blood sample will be taken by venepuncture at baseline, day 7 and 28 for antimalarial drug assay. If a child presents with fever or has a positive blood film for malaria at other times, a single blood sample will also be taken – this will normally replace the day 28 sample if there is a re-infection/recrudescence which means the child has reached a pre-specified endpoint. The total volume of blood taken from any child will be <15 mL over 6 weeks. Although there is evidence that Day 7 plasma drug concentrations are independently associated with response for lumefantrine- and PQ-based ACT,25 there has been no study that has looked at pyronaridine or naphthoquine, or simultaneously incorporated other potentially important variables such as baseline *P. falciparum* parasitaemia in predictive models. Our finding that baseline parasitaemia predicted outcome in DP-treated patients8 should also be assessed simultaneously with other parasite- and drug-specific factors in a large patient sample and using other long-half life partner drugs. We did not identify anthropometric features that predicted outcome in our previous trial and postulate the same result with the newer regimens. Plasma drug concentrations at the time of treatment failure have been used qualitatively to identify resistant parasites, but no formal *in vivo* MIC estimate the has been derived.25

We have developed high performance liquid chromatography assays for lumefantrine, naphthoquine and pyronaridine,but now have access to liquid chromatography-mass spectrometry which allows greater assay sensitivity with a smaller sample volume and increased throughput. Day 7 and follow-up samples on the day of reappearance of parasitaemia will be taken from trial patients, centrifuged promptly, and separated plasma kept and transported frozen until assayed at Curtin University. Batches of each treatment will also be retained for assay of content. We have *in vitro* parasite culture facilities at Yagaum and these can be set up at Vunapope. We will utilise the *Plasmodium* lactate dehydrogenase colorimetric assay for drug sensitivity testing.

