Kaplan-Meier estimates will be computed for each endpoint by parasite species. Treatments will be compared by log-rank test. Safety and tolerability will be assessed from the incidence of symptoms/signs to Day 7 using Poisson regression (frequent events) or Fisher’s exact test (infrequent events). Blinded interim efficacy analyses and safety assessments will be performed under the auspices of the DSMC and the trial terminated prematurely if one treatment violates the non-inferiority margin or unexpected toxicity emerges. Comprehensive health care cost data will be collected for each patient from Day 0 to Day 42 as is being done currently for the previous trial,8 but indirect costs (e.g. reduced parental/guardian income due to the child’s illness) will also be ascertained in the present trial.

Cox regression using backward-stepwise modelling will be used to determine predictors of treatment failure among age, sex, measures of growth/nutrition, baseline haemoglobin, baseline parasitaemia, Day 7 partner drug concentrations and drug-specific IC50 values. We will utilise population pharmacokinetic modelling using NONMEM (Project Group, University of California San Francisco) and models of *P. falciparum* parasite development based on our animal studies to estimate MIC and derive secondary variables of clinical importance such as the time, in 48-hour parasite life-cycles, above MIC. We have performed host genotyping for red cell traits including thalassemia, South-east Asian ovalocytosis and Gerbich antigen blood group as predictors of response in previous studies and may, if other relevant pharmacogenetic data emerge, extend the proposed analyses to include other polymorphisms.

*Duration/feasibility:* The trial will run from June 2010 to June 2013. We recruited 742 eligible children at Alexishafen and Kunjingini in the East Sepik over 2.3 years in the initial trial,8 and foresee no difficulties in recruiting 870 children to the present study over 3 years. The longer time period for the new study allows for the effect of reduced local transmission when AL is introduced.

**Sub-study 1: Effect of treatment on gametocyte carriage during follow-up** *(Secondary Aim 3)*

*Hypotheses:* i) High field gradient magnetic fractionation (HFGMF) can be used to develop a simple but sensitive field test for gametocyte transmission; ii) AL, AP and AN have similar effects on gametocyte carriage for both *P. falciparum* and *P. vivax* infections.

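### The treatment comparisons could be made somewhat more precise at almost no cost by fixing Day 0 parasite density as a covariate beside the unadjusted log-rank test

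*Protocol*

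**What the plan says.** All references are to the protocol's Research Plan, Main Study.

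- **Data analysis.** Kaplan-Meier estimates are made for each endpoint by species, and then "Treatments will be compared by log-rank test". No covariate or stratification factor is named.
- **Subjects.** Entry requires a minimum asexual density on the screening film: above 1000/μL for *P. falciparum* or above 250/μL for *P. vivax*. No upper limit on density is given.
- **Clinical/laboratory procedures.** The investigators cite "Our finding that baseline parasitaemia predicted outcome in DP-treated patients" and want this examined together with other factors and other long half-life partner drugs.
- **Data analysis, next paragraph.** Density reappears in a separate exercise: "Cox regression using backward-stepwise modelling will be used to determine predictors of treatment failure among age, sex". The rest of that candidate list includes baseline parasitaemia, Day 7 partner drug concentration and drug-specific IC50.
- **Endpoints.** The other secondary endpoints include "initial fever and parasite clearance times".

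**The concern.** A variable that is measured in every child before allocation, and that the investigators think may be prognostic, plays no part in the named treatment comparison. Its only stated use is in the predictor search. That search cannot stand in for an adjusted comparison: its covariates are chosen by the data, and one candidate, the Day 7 drug concentration, is measured after randomisation and depends on the arm.

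If density does predict the endpoint, leaving it out gives up some precision and leaves chance imbalance between arms uncorrected. That matters most in the *P. vivax* arms, which hold about 45 evaluable children each after the planned attrition. The case is most direct for parasite clearance time, because a child who starts with more parasites has further to fall before a film is negative.

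**Working it through.** **Inputs (Sample sizes section)**
- *P. falciparum*: "ACPR for AL is 95.2%8 with a non-inferiority margin of 5% for AP and AN" (the 8 after 95.2% is a reference number), 220 per group with drop-outs, one-sided 5%. A true difference of zero is assumed here.
- *P. vivax*: "uncorrected ACPR for AP and AN is at least double the 30.3% found previously for AL", so 30.3% against 60.6%; 60 per group with drop-outs, two-sided 5%.
- Both: "there will be equal numbers in each treatment arm" and "there will be a 25% attrition rate". Evaluable per arm: 220 × 0.75 = 165 and 60 × 0.75 = 45.
- Strength of density as a predictor: not in the documents. Assumed odds ratio (OR) per SD of log density: 1.25 to 3.

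**The plan's own figures**

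The table states power above 80% and above 90%. With no losses, 220 per arm gives 79.1% and 60 per arm gives 92.5%. After 25% attrition the unadjusted starting points are as follows.
- *P. falciparum*: SE = √(2 × 0.952 × 0.048 / 165) = 0.02353. Power = Φ(0.05/0.02353 − 1.645) = Φ(0.480) = 68.4%.
- *P. vivax*, pooled-variance test, mean proportion 0.4545: Φ[(0.303√45 − 1.96√(2 × 0.4545 × 0.5455)) / √(0.2112 + 0.2388)] = Φ(0.973) = 83.5%.
- *P. vivax*, unpooled: SE = √(0.44996/45) = 0.1000. Power = Φ(3.030 − 1.96) = 85.8%.
- *P. vivax*, log-rank approximation: hazard ratio = ln 0.606 / ln 0.303 = 0.419; events = 45 × (0.697 + 0.394) = 49.1. Power = Φ(√(49.1/4) × 0.869 − 1.96) = 86.1%.

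**Effect of adjustment**

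The variance is multiplied by (1 − R²), with R² taken from a logistic model with one normal covariate at the stated failure rate (4.8% for *P. falciparum*, mean 54.55% for *P. vivax*). The *P. vivax* power column uses the pooled-variance test.

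| OR per SD | R², *P. falciparum* | Power, 165/arm | R², *P. vivax* | Power, 45/arm |
|---|---|---|---|---|
| none | 0 | 68.4% | 0 | 83.5% |
| 1.25 | 0.2% | 68.5% | 1.2% | 83.9% |
| 1.5 | 0.8% | 68.7% | 3.8% | 84.9% |
| 2 | 2.5% | 69.4% | 9.8% | 87.1% |
| 3 | 6.9% | 71.1% | 19.7% | 90.7% |

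On the unpooled formula, the *P. vivax* figure goes from 85.8% to between about 86% and 92%.

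As a cross-check, simulated Cox tests of treatment at 45 per arm, with and without the covariate, gave:
- 85.6% to 86.7% at a hazard ratio of 1.25 per SD;
- 85.7% to 89.0% at 1.5;
- 86.7% to 94.0% at 2.

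That is a gain of about 1 to 7 points, in line with the table.

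**Why *P. falciparum* gains little.** Expected failures are 165 × 0.048 = 7.9 per arm. At so low a rate, even a strong predictor explains little of the variance of the outcome.

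**Clearance time.** If density falls log-linearly at rate *k* to a detection limit *L*, clearance time is (log D₀ − log *L*)/*k*. Starting density then enters the endpoint directly, and entry sets only a floor on it. The protocol does not state log-linear clearance, and films are scheduled only on Days 1, 2, 3 and 7, so times are coarse and heavily tied. An illustrative simulation on that visit grid still gained about 5 to 7 points of power. Its clearance inputs are assumed, so this is an indication only.

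**The case against.** **Nothing is invalid.** An unadjusted log-rank test in a randomised trial controls type I error. The protocol refers to an a priori analysis plan that is not at hand, and covariates are commonly settled there. This stands: a reader might infer bias or a mistake, and the documents support neither. What remains is that the protocol itself names the comparison and gives density a different role, so the suggestion is specific.

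**Density is not an established predictor here.** The reported finding concerns DP recipients in an earlier trial. DP is not an initial arm; it enters only if artemisinin-naphthoquine is withdrawn. The species is not stated, and the sentence before it speaks of *P. falciparum* density. No section says that Day 0 *P. vivax* density predicts reappearance of *P. vivax*. This also stands. For the three regimens under test, the association is a plausible question without a stated size.

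**A large gain for *P. falciparum* is tempting to claim.** It would need a correlation of 0.35 to 0.5 between density and failure. At 4.8% failures that means an OR per SD of about 4.2 to 8.6, and nothing in the documents supports so strong a predictor.

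**Adjustment might seem to answer the low power.** A reader might infer that it brings the comparisons up to their stated power. For *P. falciparum*, 80% at 165 per arm needs an R² of about 27% (1 − 165/227, where 227 evaluable per arm give 80%). The highest value in the table is 6.9%. The shortfall is a separate sample-size matter.

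**Conclusion.** This is an optional improvement in efficiency, not an error. The text supports three facts: density is known for every child, the only named treatment comparison is unadjusted, and the predictor search is not a substitute for an adjusted comparison. The text does not support bias, an established prognostic effect under the trial regimens, or a cure for low power.

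For an assumed OR per SD of 1.25 to 3, the gain is about 0.5 to 7 points for *P. vivax* and about 0 to 3 points for *P. falciparum*. These figures assume 25% attrition, the planned response rates and a single normally distributed log-density covariate. If density proves unrelated to outcome, the gain is essentially nil. Parasite clearance time has the clearest mechanism, although its gain rests on assumed log-linear clearance.

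**What to change.** - Pre-specify log10 Day 0 asexual density of the treated species as a fixed covariate in a Cox comparison of treatments, for the *P. vivax* primary endpoint and the time-to-event secondary endpoints, above all parasite clearance time. State how tied times are handled.
- Keep the log-rank test and Kaplan-Meier estimates as the unadjusted analysis.
- State that the covariate is fixed in advance and is not chosen by the backward-stepwise model, and that Day 7 drug concentration does not enter the treatment comparison.
- For *P. falciparum* non-inferiority, adjustment is optional. If it is done, use a covariate-standardised difference in Day 42 PCR-corrected response, so that the 5-point margin keeps its meaning.

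The cost is wording in the protocol or analysis plan; no extra visits, samples or children are needed. The one drawback is that the Cox hazard ratio is conditional on density, so the unadjusted results must be shown beside it.

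### The falciparum comparison is designed as non-inferiority with a 5-point margin, but the only efficacy test the protocol names is an ordinary log-rank test, which uses no margin

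*Protocol*

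**What the plan says.** All of this is in the Protocol, RESEARCH PLAN, Main Study.

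- *Sample sizes.* The falciparum calculation assumes "Day 42 PCR-corrected ACPR for AL is 95.2"%, "with a non-inferiority margin of 5% for AP and AN". The table row reads "Non-inferiority | 515 | 220 | >80% | 0.05 (one-tailed"). The vivax row is a superiority comparison at two-tailed 0.05.
- *Data analysis.* Kaplan-Meier estimates are planned for each endpoint, separately by species. The next sentence is "Treatments will be compared by log-rank test". It does not distinguish falciparum from vivax and mentions no margin, confidence bound or shifted null hypothesis.
- *Data analysis, later in the same paragraph.* The margin returns as a ground for ending the trial early. How a breach would be assessed is not stated.
- *Other named methods.* Poisson regression and Fisher's exact test are for safety and tolerability. Cox regression is for predictors of failure and for Sub-study 2. None is assigned to the falciparum non-inferiority comparison.
- *Analysis sets.* A per-protocol analysis is accompanied by two modified intention-to-treat versions: a worst case and "a best-case approach (all missing blood films assumed parasite-negative").

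**The concern.** The null hypothesis of an ordinary log-rank test is that the arms have the same failure-time curve. The design needs the opposite null, that the new ACT is at least 5 points worse than AL, and needs evidence against it. A non-significant log-rank result says only that a difference was not detected. With few failures expected in each arm, that is a likely outcome even when the new drug lies at or beyond the margin.

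The falciparum comparison is one of the two primary questions, and the *Ethical issues* section links the trial to future treatment policy in PNG children. If the analysis followed the protocol text literally, the primary falciparum question would have a p-value that does not answer it. The natural summary of a non-significant result, that the new ACT did not differ from AL, could be given to a drug that fails the trial's own criterion.

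**Working it through.** **Inputs.** From *Sample sizes*: AL efficacy 95.2%, margin 5% (read as absolute points; the scale is not spelled out), one-sided alpha 0.05, power above 80%, 25% attrition, and "there will be equal numbers in each treatment arm". Assumption: AP and AN equal AL under the design alternative (not stated).

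**The plan's own figure.** For two proportions both at 0.952 with margin 0.05, a score-type calculation (Farrington-Manning) uses rates restricted to the margin of 0.9668 and 0.9168:

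n = [1.645 × √(0.9668×0.0332 + 0.9168×0.0832) + 0.842 × √(2×0.952×0.048)]² / 0.05² ≈ 253.4, so 254 per arm and about 507 for two arms.

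This is within 3% of 515, so 515 is recognisable as a two-arm non-inferiority total of about 258 per arm. The sample size therefore does rest on a margin comparison of Day-42 proportions. The 220 per group with drop-outs leaves 220 × 0.75 = 165 evaluable. Because 258 and 165 do not agree, results are shown at 165, 220 and 258. Whether those sizes are adequate is a separate matter.

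**How often a difference test misses a drug at the margin.** A pooled two-proportion z test at two-sided 0.05 stands in for log-rank, with true rates 0.952 and 0.902 (mean 0.927). At 165 per arm:

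- SE under equality: √(2×0.927×0.073/165) = 0.0286
- SE under the true rates: √((0.952×0.048 + 0.902×0.098)/165) = 0.0285
- Power: Φ((0.05 − 1.96×0.0286)/0.0285) = Φ(−0.215) = 0.415, so about 58.5% of trials are non-significant.

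Exact binomial enumeration over all pairs of failure counts gives:

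| Evaluable per arm | Non-significant difference test | Passes the one-sided 95% bound against 5 points |
| --- | --- | --- |
| 165 | 58.5% | 5.5% |
| 220 | 47.6% | 5.8% |
| 258 | 40.2% | 5.6% |

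The last column uses the unpooled (Wald) bound. At 165 per arm and a true rate of 88.0% (7.2 points worse), about 33% of trials are still non-significant.

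**Under true equality** (both 0.952, 165 per arm), about 29% of trials are non-significant yet fail the 5-point bound.

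**A single data set.** Take 165 per arm and 8 AL failures (165 × 0.048 = 7.9). The upper bound for the failure difference is d + 1.645 × √(Σ p(1−p)/165).

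- 9 failures in the new arm: 0.61 + 1.645 × 2.43 = 4.6 points, which meets the margin.
- 10 failures: 1.21 + 1.645 × 2.50 = 5.3 points, which fails.
- 17 failures: the difference test gives p = 0.061; at 18 it gives p = 0.041.

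So 10 to 17 failures would be not significantly different from AL and yet fail the design criterion.

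**Analysis sets.** If 25% of each arm is lost and every lost child receives the same imputed outcome, a true 5-point gap becomes 5 × 0.75 = 3.75 points. This applies to the best case and the worst case alike.

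**The case against.** *The protocol defers to an a priori plan that is not at hand.* A decision rule for non-inferiority is often left to such a plan, and its absence alone would be no finding. But the protocol does name a method for comparing treatments, and that method does not fit the falciparum hypothesis. A plan that follows the text inherits the mismatch; one that adds a margin rule departs from the text.

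*The margin is not forgotten.* The early-stopping sentence applies it to trial data, and Kaplan-Meier estimates are already planned. This stands: a margin comparison was evidently in mind, and the quantity needed for it will exist. What is missing is the link between that quantity, the margin and the conclusion.

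*The error rates depend on a rule that the protocol does not contain.* This also stands. A reader might infer that a non-significant log-rank result will be declared non-inferior, or even that log-rank is designated the primary non-inferiority test. The text says neither. The 40% to 59% describes that misreading and is not the type I error of a stated rule.

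*Three further inferences go too far.* A log-rank-type test with a shifted null could establish non-inferiority, but it would need a hazard-ratio margin (ln 0.902 / ln 0.952 ≈ 2.10 under proportional hazards), and none is given. A significantly worse result that still meets the margin is possible in principle but occurs in about 0.01% of trials or fewer at the planned rates. The imputation rules might be read as biasing the primary result, but they accompany a per-protocol analysis and nothing says the best case alone decides.

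**Conclusion.** The point holds in this form: the stated efficacy test does not match the stated falciparum hypothesis, and no other stated method fills the gap. The log-rank sentence is right for vivax superiority and incomplete for falciparum.

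The size is conditional. If non-significance were taken as no worse than AL, a drug exactly at the margin would escape in roughly 40% to 59% of trials, depending on whether 258 or 165 per arm are evaluable. The intended error is 5%. The figures assume AL at 95.2%, an absolute 5-point margin and a two-proportion stand-in for log-rank; no log-rank simulation was run. The mismatch itself depends on none of these numbers.

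**What to change.** In *Data analysis*, replace the single log-rank sentence with text to this effect:

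- For falciparum, the AP-minus-AL and AN-minus-AL differences in Day-42 PCR-corrected efficacy, taken from the planned Kaplan-Meier estimates, are each reported with a one-sided 95% lower confidence bound. Non-inferiority is declared only if that bound lies above -5 percentage points.
- The log-rank test is kept for the vivax superiority comparison and as support for the secondary endpoints.
- The per-protocol and best-case and worst-case modified intention-to-treat sets stay as planned, but the non-inferiority conclusion does not rest on the best-case imputation alone, because equal imputation in every arm shrinks the difference.

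If an analysis plan already contains such a rule, the protocol sentence should be brought into line with it. The cost is a few sentences. No new data are needed, and this change does not alter the sample size, which was already calculated for a margin comparison.
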